#### MRT Sample Size Calculation

To address the objective of exploring CliMACT training components as specific active ingredients, an MRT will be conducted. Based on the power approximation for MRTs [85,86], a sample size of 25 participants is sufficient to detect a small effect size of *d* ≥0.15 on a proximal EMA outcome, with *t*=252 decision points (based on our EMIs with a training duration of 42 days with 6 random EMA prompts per day) and a power of 80% for a 2-sided test α=.05, with an availability rate η (ie, proportion of completed EMA observations at given decision point T) of 50% and a randomization probability of 0.85 (ie, a ratio of 6:1 for experimental vs control components).

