As nonspecific active ingredients (objective 2 continued), we will explore the association of working alliance toward mental health professionals as well as working alliance with the app-based EMI with the 8 candidate outcomes in participants of the experimental condition, using linear mixed models. Separate models will be fitted for each alliance type and candidate outcome at both posttraining and 4-week follow-up; additionally, time (posttraining and 4-week follow-up), the respective outcome at baseline, and working alliance will be entered as independent variables (details set in preregistered statistical analysis plan, becoming public on OSF after publication of results) [87]. A level-2 random intercept for subject and a random effect for time will be added, and level-1 residuals will be allowed to be correlated to account for within-subject nesting of repeated measures. For the 2 momentary outcomes of nonspecific active ingredients, outcomes measured at baseline will be person-mean centered, and, in addition to the above specifications, random slopes for time and working alliance will be added, with an unstructured variance-covariance matrix. Within-subject residuals will be modeled with an autoregressive structure of the exponential type, allowing the models to account for unequally spaced time values. Restricted maximum likelihood estimation will be applied.

As specific active ingredients (objective 2 continued), we will explore proximal effects of CFI-based CliMACT training components on momentary negative affect in an MRT design in participants in the experimental condition using linear mixed modeling. MRT condition (experimental: any adaptive CFI-based training component vs control: no adaptive training component, randomized at a ratio of 6:1 in moments of higher negative affect), negative affect at *t*_n_ (person-mean centered), and time between assessment time points will be entered as independent variables. Negative affect at *t*_n+1_ will be entered as the dependent variable. A level-2 random intercept will be added, and level-1 residuals will be allowed to be correlated to account for within-subject nesting of repeated measures. Restricted maximum likelihood estimation will be applied.

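### The MRT model lets neither the condition effect vary between participants nor its standard error allow for it, so its 95% CI is too narrow if participants respond differently

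*Protocol article*

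**What the plan says.** Under Statistical Analysis, Feasibility, the article sets out the model for specific active ingredients. The outcome is negative affect at the next assessment. The predictors are MRT condition (any adaptive component against none, 6:1), "negative affect at *t*_n_ (person-mean centered), and time between assessment time points will be entered as independent variables". The dependence structure is given in one sentence: "A level-2 random intercept will be added, and level-1 residuals will be allowed to be correlated", with the nesting of repeated measures as the reason. The estimation method follows: "Restricted maximum likelihood estimation will be applied". No random slope for condition and no clustered or robust standard error is named.

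In the preceding paragraph, the momentary working-alliance models are specified differently: "random slopes for time and working alliance will be added, with an unstructured variance-covariance matrix".

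The MRT Sample Size Calculation states that "a sample size of 25 participants is sufficient to detect a small effect size of *d* ≥0.15 on a proximal EMA outcome", using 252 decision points, 50% availability, randomization probability 0.85, 80% power and two-sided alpha 0.05. Under Randomization and Blinding, randomization takes place only when the negative-affect threshold is exceeded. Under Initial Signals of Efficacy, 95% CIs are to be inspected for all analyses because these are exploratory.

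**The concern.** MRT condition is randomized repeatedly within each person, so each participant has an individual effect. If those effects differ, the average over 25 people carries sampling error from which people were enrolled, and more prompts per person do not remove it. A random intercept absorbs differences in level, not in effect. Serially correlated residuals fade with lag, whereas a person's own effect applies at every treated moment. The stated model therefore treats all moments as estimating one common effect.

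At stake is the article's only randomized evidence on specific active ingredients and the only analysis with a stated power. The CI is its inferential tool, and the Discussion says that findings on delivery will be used to improve training components. That use reaches beyond these 25 participants.

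**Working it through.** **Inputs from the article.** N = 25; 252 decision points × 0.50 availability = 126 answered prompts per person; ρ = 0.85; d = 0.15.

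**Assumptions.** τ, the between-person SD of the condition effect in outcome SD units, is not given; 0 to 0.30 is shown. The share of prompts above the threshold is not given either. Besides 126, I use 39 and 25 randomized points per person (31% and 20% of 126). Points are taken as equal across people.

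**The plan's own figure.** Noncentrality = N × m × ρ(1−ρ) × d² = 25 × 126 × 0.1275 × 0.0225 = 9.04. An F test with 1 and N−q−1 df (q = 1 to 3) gives power 0.818 to 0.821. With the exact 6:1 ratio, ρ(1−ρ) = 0.1224, noncentrality is 8.68 and power is 0.802 to 0.805. The stated 25 reproduces, on a formula with no between-person variance in the effect.

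**What the model's standard error leaves out.**

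Var(estimate) = 1/[N m ρ(1−ρ)] + τ²/N

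The stated model reports only the first term. With m = 126 that is 1/401.6, so the SE is 0.0499 whatever τ is. Adding the second term:
- τ = 0.15: √(0.00249 + 0.0225/25) = √0.00339 = 0.0582, 17% larger.
- τ = 0.30: √(0.00249 + 0.09/25) = √0.00609 = 0.0780, 56% larger.

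Coverage of the nominal 95% CI = 2Φ(1.96 × model SE / full SE) − 1:

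| Points per person | τ = 0.05 | τ = 0.075 | τ = 0.15 | τ = 0.30 |
|---|---|---|---|---|
| 126 | 94.5% | 93.9% | 90.7% | 79.0% |
| 39 | 94.9% | 94.7% | 93.7% | 89.7% |
| 25 | 94.9% | 94.8% | 94.2% | 91.6% |

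**Simulation.** With N = 25, 6:1 randomization and independent residuals, random-intercept coverage at τ = 0.15 / 0.30 was about 91% / 80% at 126 points, 94% / 89% at 39 and 94.5% / 92% at 25, in line with the formula. Participant-clustered SEs with a leverage correction and t on 24 df stayed at about 94 to 95%, including at τ = 0.

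**Do correlated residuals repair it?** With AR(1) residuals, REML, 126 points and τ = 0.15 (400 runs), the mean model SE was 0.0459 against an empirical SD of 0.0541, and coverage was 90.2%. Adding a random slope for condition gave a mean SE of 0.0553 and coverage of 94.0%. Only τ = 0.15 was completed for this variant.

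**The case against.** The strongest objection is that variance estimators and reference df are usually left to the analysis plan. The article cites a preregistered plan that is not shown, and it neither states nor excludes clustered errors. This stands only in part. The article gives the MRT model's fixed effects, random effects, residual structure and estimator, and on that specification the CI has the weakness shown. If the unseen plan already names a random slope or clustered errors, the point is met.

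The second objection stands in full: τ appears nowhere in the documents. Values of 0.15 and 0.30 equal and double the target d. With normal effects averaging 0.15, they would mean that 16% (Φ(−1)) and 31% (Φ(−0.5)) of participants are made worse. Much smaller values are possible.

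The third also stands: 126 counts every answered prompt, while randomization needs the threshold to be exceeded and the outcome needs a next rating. Fewer points mean that ordinary sampling error dominates and the shortfall shrinks.

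A reader might infer from the random slopes in other momentary models that the article contradicts itself. It does not. Those slopes are for time, working alliance, or the candidate mechanism or outcome, and none is for a randomized condition. They do show that the authors name random slopes where they intend them.

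Finally, for the average effect in these 25 participants alone, the interval is about right. The shortfall concerns the wider population.

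**Conclusion.** The point holds conditionally. As specified, the model's CI omits τ²/N and is too narrow for the population-average proximal effect whenever τ exceeds zero; correlated residuals do not correct this. In practice the loss is negligible up to τ of about 0.075. It becomes material from about 0.15 if the number of randomized points is near the upper bound of 126, and it is modest at 25 to 39 points unless τ is near 0.30.

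A reader might conclude that coverage will be near 80%, or that 25 participants is a wrong sample size. The documents support neither. The first needs both the largest τ and the upper-bound number of points. The stated 25 reproduces on its own assumptions, and no τ is given from which to revise it.

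The analysis is exploratory and Table 1 has no MRT criterion. Priority is low to moderate.

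**What to change.** Keep the stated mean model. Report the MRT condition effect with participant-clustered standard errors, a small-sample correction and a t reference on about 24 df. If the REML routine does not offer clustered errors, use an estimator that does. Alternatively, add an uncorrelated random slope for MRT condition under REML with small-sample df, keeping the clustered interval as fallback if the slope model does not converge.

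The cost is one sentence in the analysis plan and a few lines of code. If effects do not vary, the clustered interval is about 5% wider, from the t(24) quantile alone (2.064/1.960 = 1.05). Data collection is complete, but only the analysis changes. If analysis has already begun, report the result as a declared sensitivity analysis.

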#### Initial Signals of Efficacy on Candidate Outcomes and Mechanisms

Initial signals of efficacy of the CliMACT training will be explored according to the intention-to-treat principle (ie, data of all participants randomized to 1 of the 2 conditions will be entered into the analysis). Before data analysis, all data will be checked for quality and plausibility. For all analyses, we will inspect the 95% CI and obtain d-type effect sizes given their exploratory nature. Linear mixed modeling will be used to compare candidate outcomes (objective 3) and candidate mechanisms (objective 4) between the experimental and control conditions at posttraining and 4-week follow-up. Each candidate outcome and mechanism (applying joint analyses to posttraining and 4-week follow-up assessment) will be used as a dependent variable in separate analyses. Time (posttraining and 4-week follow-up), condition (experimental and control condition), and the respective outcome measured at baseline (grand-mean centered) will be entered as independent variables. A level-2 random intercept will be added, and level-1 residuals will be allowed to be correlated to account for within-subject nesting of repeated measures. Restricted maximum likelihood estimation will be applied. The coefficient for the condition reflects the difference between the intervention and control arm for the post- and 4-week follow-up assessments jointly. We will next extend the model by a condition × time interaction to determine the time-specific contrasts, reflecting differences between the 2 conditions at each time point, and an outcome or mechanism at baseline × time interaction.

Model specifications for momentary outcomes and mechanisms are as follows. The respective putative mechanism (momentary value-based living, momentary emotional resilience, momentary self-efficacy, and momentary PEB) or outcome (positive affect, negative affect, climate change distress, and climate change impairment) as measured 8 times per day on 6 consecutive days will be entered as dependent variables in separate models. As independent variables, the respective candidate EMA-based mechanism or outcome at baseline (person-mean-centered), time, condition, a mechanism or outcome at baseline × time interaction, and a condition × time interaction are entered. A 2-level model will be estimated with time points nested in participants. Random intercepts will be included for participant and time point. Random slopes will be included for time and the respective candidate mechanism or outcome, applying an unstructured variance-covariance matrix. For EMA observations at each time point (posttraining and 4-week follow-up), we assume within-subject residuals to be autocorrelated and apply an autoregressive structure of the exponential type. Hours since midnight of the first EMA day are used as a time indicator in our models. This approach, in contrast to using the beep number, accounts for unequally spaced delays between beeps. Again, restricted maximum likelihood estimation will be applied. Next, the respective model will, again, be extended by a condition × time interaction in order to determine the time-specific contrasts, reflecting differences between the 2 conditions at each time point.

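### The momentary (EMA) models person-mean-centre the baseline value, so they do not adjust for participants' baseline level

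*Protocol article*

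**What the plan says.** The article specifies baseline terms in four places, all under Statistical Analysis.

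- **Questionnaire outcomes and mechanisms** (Initial Signals of Efficacy): "the respective outcome measured at baseline (grand-mean centered) will be entered as independent variables", alongside time and condition.
- **Momentary outcomes and mechanisms** (same section, 4 outcomes and 4 mechanisms, "as measured 8 times per day on 6 consecutive days"): the independent variables include "the respective candidate EMA-based mechanism or outcome at baseline (person-mean-centered), time, condition", plus interactions of baseline and of condition with time. The random part is described by "A 2-level model will be estimated with time points nested in participants" and "Random slopes will be included for time and the respective candidate mechanism or outcome".
- **Working-alliance models for the 2 momentary outcomes** (Feasibility): "outcomes measured at baseline will be person-mean centered". The random slopes here are for time and alliance.
- **Microrandomised comparison** (Feasibility): negative affect at the current prompt is entered "person-mean centered), and time between assessment time points will be entered as independent variables".

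Neither set of momentary models adds the participant's own baseline mean as a separate covariate. The article gives no reason for centring differently from the questionnaire models.

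**The concern.** The dependent variables are EMA ratings after training and at the 4-week follow-up. Condition varies only between participants, so its effect is estimated from differences between participants. A baseline covariate helps that contrast only if it also varies between participants. Person-mean centring removes exactly that variation.

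Two things are at stake. First, the Discussion says that effect size estimates will support the choice of a primary outcome for the definitive trial, and that measures will be prioritised by their efficacy signals. As written, questionnaire measures compete with baseline adjustment and EMA measures without it, so the EMA signals are noisier and carry any chance imbalance. Second, the alliance models have no randomisation to rely on. Alliance is measured at post-training, in the experimental arm only. An association with later affect or distress may simply reflect where participants started.

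**Working it through.** **Inputs from the article.** At most 50 participants, 25 per arm (Justification of Sample Size). Prompts per EMA period: 8 × 6 = 48. The article states no standard error, power or baseline correlation for these models, so there is no published figure to reproduce.

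**Assumptions, not in the article.** Person-level baseline-to-follow-up correlation r, shown over 0.4 to 0.8. Intraclass correlation of 0.4 where measurement error or simulation enters.

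**Step 1: what the centred term contains.** Let x_ij be participant i's baseline rating at prompt j, and m_i that participant's baseline mean.

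- One baseline value per participant: m_i − m_i = 0 for everyone. The covariate is a column of zeros, and its coefficient, time interaction and random slope cannot be estimated.
- Prompt-level values: the mean over j of (x_ij − m_i) is 0 for everyone. With complete data the term is orthogonal to condition and to any other participant-level variable.

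The time interaction and the random slope are built from the same centred variable and do not bring m_i back. A random intercept allows participants to differ but does not remove a baseline difference between arms.

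This step needs no numerical assumption.

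**Step 2: precision forgone.** Adjusting for a baseline mean multiplies the standard error of the condition effect by √(1 − r²), so the unadjusted interval is wider by the factor 1/√(1 − r²).

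With measurement error, the reliability of a 48-prompt mean at intraclass correlation 0.4 is 0.4 / (0.4 + 0.6/48) = 0.4 / 0.4125 = 0.970, and r is replaced by 0.970 r.

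| r (assumed) | Width factor, no measurement error | Width factor, reliability 0.970 |
|---|---|---|
| 0.4 | 1/√0.84 = 1.09 | 1/0.922 = 1.08 |
| 0.6 | 1/√0.64 = 1.25 | 1/0.813 = 1.23 |
| 0.8 | 1/√0.36 = 1.67 | 1/0.631 = 1.58 |

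**Step 3: chance imbalance.** The SD of the between-arm difference in baseline level, in person-level SD units, is √(1/25 + 1/25) = √0.08 = 0.28.

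**Step 4: simulation check.** Random-intercept models fitted by restricted maximum likelihood, 25 per arm, 48 prompts, no true effect, r = 0.6, intraclass correlation 0.4, 60 replicates per scenario. The set-up is simplified: one post-training wave, no random slopes, no autoregressive residuals. Effects are in total-SD units of the outcome.

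| Quantity | No baseline term | Person-mean-centred | Participant mean, grand-mean centred |
|---|---|---|---|
| Mean SE, complete data | 0.181 | 0.181 | 0.146 |
| Mean SE, 30% of prompts missing | 0.186 | 0.186 | 0.155 |
| Mean estimate, forced baseline imbalance of 0.5 person-level SD | 0.205 | 0.205 | 0.019 |

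With complete data, the estimate using the person-mean-centred term matched the estimate with no baseline term in every replicate. With 30% missing the largest difference was about 0.002. The SE ratio 0.181/0.146 = 1.24 agrees with the 1.23 in step 2. The forced-imbalance estimate is close to its expected value, 0.6 × 0.5 × √0.4 = 0.19.

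**The case against.** **Loose wording.** The authors may have meant person means, centred across participants. The article's own usage speaks against this. It names grand-mean centring for the questionnaires, and it uses person-mean centring in the ordinary within-person sense for the microrandomised comparison, where it is appropriate. If the other meaning was intended, the text still needs correcting.

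**Detail left to the analysis plan.** A preregistered plan exists and is not shown. But the article states this specification itself, so the point concerns what is written and not something left out.

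**The term is not empty.** This stands in part. Prompt-level deviations could absorb within-person patterns such as time of day, if baseline prompts were paired with later ones. The article gives no pairing rule and may leave it to the plan. A reader might infer that the term does nothing at all, but the supportable claim is narrower: it does not adjust for baseline level.

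**The efficacy estimates are biased.** A reader might infer this from the forced-imbalance result. The documents do not support it. Allocation is randomised, so the contrast without baseline adjustment is unbiased on average. The simulated 0.205 arises because the imbalance was imposed.

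**All alliance models are affected.** This also goes too far. Person-mean centring is stated only for the 2 momentary outcomes. The other alliance models enter the baseline outcome without it.

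**The analyses are exploratory.** This stands and limits the severity. The primary objective is recruitment feasibility, no traffic-light criterion uses these models, and the Discussion concedes that effect sizes will remain uncertain.

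**Conclusion.** The point holds. As written, the 8 momentary efficacy models and the alliance models for the 2 momentary outcomes are not adjusted for participants' baseline level. That follows from algebra alone.

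The size of the loss depends on a correlation that the article does not give. The range of about 9% to 67% wider intervals, somewhat less with measurement error, is illustrative. For the efficacy contrasts the cost is precision and lack of protection against chance imbalance. For the momentary alliance models, confounding by baseline level is added.

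This should be fixed, but it does not threaten the trial's main conclusions. It matters because these effect sizes feed into the choice of primary outcome for the definitive trial.

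**What to change.** In the momentary efficacy models, and in the alliance models for the 2 momentary outcomes:

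- Replace the person-mean-centred baseline term with each participant's mean over the 6-day baseline EMA, grand-mean centred, as a level-2 covariate.
- Keep its interaction with time point where one is planned.
- In the momentary efficacy models only, drop the random slope on this covariate, because a covariate with one value per participant cannot support a participant-specific slope. The alliance models have no such slope to remove.

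The change needs only wording and code, since the baseline EMA data are already collected. There is a small procedural cost: data collection is complete and a preregistered analysis plan exists. Record the change as a dated amendment, if possible before the analysts are unblinded, and report the published specification as a sensitivity analysis wherever it can be estimated.

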#### Subgroup Analyses by Marginalized/Vulnerable Group Status

To address the objective of examining the feasibility of establishing credibility criteria for a priori planned subgroup analyses (objective 5), we will explore the feasibility of generating a marginalized/vulnerable group status score by, first, descriptively exploring the distribution of indicators for health inequities relevant to climate change–related distress as a basis for subgroup analyses (family SES, level of education, sex, migrant status, ethnic minority status, and current urbanicity) in the sample. Second, descriptively exploring the distribution of a combined marginalized/vulnerable group status variable (indicated by any of the following characteristics: family SES=low, level of education=lower, gender≠male, migrant status=yes, ethnic minority status=yes, and current urbanicity=yes) and a marginalized group status variable (indicated by any of the following characteristics: family SES=low, level of education=lower, migrant status=yes, ethnic minority status=yes; thus excluding gender and current urbanicity in comparison to the combined marginalized/vulnerable group status variable). Third, conducting subgroup analyses on candidate outcomes stratified by combined marginalized/vulnerable group status (yes or no) and by marginalized group status (yes or no), as defined in the second point above.

We will use a restricted set of established credibility criteria for subgroup analyses as appropriate for this feasibility RCT [88]: (1) measuring indicators for health inequities relevant to climate change–related distress at baseline, that is, before randomization, and (2) exploring differences in effect sizes and CIs stratified by subgroups with and without marginalized/vulnerable group status.

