### This Study

This study aims to investigate the feasibility and initial signals of efficacy of the CliMACT (Climate Mind and Act) training, a novel hybrid EMI for mental health promotion in youth with climate change–related distress, in addition to access to all standard health care and social services (care as usual [CAU]), compared with CAU only in a feasibility RCT (ISRCTN33613914). Feasibility criteria are based on the principles of the CONSORT (Consolidated Standards of Reporting Trials) extension for pilot and feasibility trials [38] and adapted from the study by Reininghaus et al [16]. To achieve the overall aim, we will first, examine the feasibility of the trial methodology (based on recruitment, randomization, and retention). Second, we will examine the feasibility of delivering the CliMACT training (based on participant satisfaction, participant adherence, and fidelity to the training protocol) and explore its specific and nonspecific active ingredients (CliMACT training components; working alliance toward mental health professionals and toward the EMI). Third, we will explore signals of efficacy of the CliMACT training on candidate outcomes, that is, positive mental health (quality of life [psychological and social domain], happiness, and mental well-being), climate change distress and psychological distress, as well as on momentary affect and momentary climate change–related distress at posttraining and 4-week follow-up. Fourth, we explore signals of efficacy of the CliMACT training on candidate mechanisms of change, namely self-compassion, mindfulness, psychological inflexibility, self-efficacy, resilience, PEB, emotion regulation, internalized stigma, and experience of discrimination, self-stigma of help-seeking, as well as on momentary emotional resilience, momentary self-efficacy, momentary PEB, and momentary value-based living at posttraining and 4-week follow-up. Fifth, we examine the feasibility of establishing credibility criteria for an a priori planned subgroup analyses on social and ethnic inequities in health by exploring the distribution of indicators for health inequities relevant to climate change–related distress, and exploring the effects of the CliMACT training stratified by marginalized or vulnerable group status (defined as meeting any of the following criteria: gender not male, ethnic minority, migration history, low family SES, current urbanicity, or lower education level). Sixth, we examine the feasibility of measuring related costs of care and service use and health-related quality of life for the accompanying economic evaluation in a future definitive RCT, and explore the distribution of cost patterns across the experimental and control groups.

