#### Other Measures

At each assessment, it will be documented if any adverse events (AEs) related or unrelated to the training or study participation have occurred, including health-related events, technical problems with the smartphone, problems with the digital application, or other issues. Marginalized or vulnerable group status is reflected by equity-relevant sociodemographic indicators at baseline and coded present when at least one of the following is true: female gender, ethnic minority, migration history, low family SES, current urbanicity, and lower education level. At posttraining, adverse trial effects are measured with the measure by Hutton et al [82], using a 5-point Likert scale ranging from 1-5. An overview of all measures and time points can be found in Figure 2 (in line with the SPIRIT [Standard Protocol Items: Recommendations for Interventional Trials] statement [83]).

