### Justification of Sample Size

#### Feasibility RCT

The sample size for this feasibility RCT is primarily determined to address the primary objective to provide the basis for successful recruitment in a fully powered efficacy-effectiveness RCT. Initial sample size planning points to ≈180 participants required for the full RCT. To this end, we set a feasibility limit of a minimum monthly recruitment rate of 11 participants in (at least) the month with the highest recruitment rate of the feasibility trial recruitment period. This lower bound reflects the minimum monthly recruitment rate required to recruit an expected ≈180 participants for a subsequent fully powered RCT within a designated period of 17 months. This study’s population for the feasibility RCT will comprise a maximum of 50 youth aged 14-25 years (n=25 in the experimental and control conditions, respectively) with climate change–related distress. This upper limit of 50 is based on recommendations by Whitehead et al [84] for determining sample size for feasibility RCTs and would reflect a monthly recruitment rate of 17 if recruitment can be completed within 3 months. Thus, the feasibility trial will inform us about the feasibility of the aspired recruitment rate and the possibility of overrecruitment.

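### The marginalized/vulnerable subgroup variable has an inconsistent gender element, may leave a small comparison stratum, and is analysed by stratum without a named condition × group contrast

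*Protocol article*

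**What the plan says.** The combined variable is defined in three places in the protocol article.

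- This Study (aims) lists "gender not male, ethnic minority, migration history, low family SES, current urbanicity, or lower education level", any one being enough.
- Other Measures says that status is present if at least one of these holds: "female gender, ethnic minority, migration history, low family SES, current urbanicity, and lower education level".
- Subgroup Analyses by Marginalized/Vulnerable Group Status completes its list with "gender≠male, migrant status=yes, ethnic minority status=yes, and current urbanicity=yes". The same section first lists the indicators to be described as "family SES, level of education, sex, migrant status, ethnic minority status, and current urbanicity".

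That section sets three steps: describe the indicators; describe the combined variable and a narrower marginalized variable, "thus excluding gender and current urbanicity in comparison to the combined marginalized/vulnerable group status variable"; then analyse candidate outcomes stratified by each variable. Its second credibility criterion is "exploring differences in effect sizes and CIs stratified by subgroups with and without marginalized/vulnerable group status". No condition × group term is named. The sample is at most 50, "n=25 in the experimental and control conditions, respectively".

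**The concern.** Objective 5 asks whether a credible subgroup analysis is feasible, and the answer will shape the definitive trial. That needs a variable coded in one way, two strata large enough to compare, and a stated quantity for the difference in effect.

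On the first, the sections disagree about gender. On the second, a variable triggered by any of six traits, two of which (not being male, living in an urban area) may be common in this sample, could leave few participants unexposed. The third step nevertheless goes ahead whatever the first two show. On the third, two effects with two intervals side by side tempt the reader to infer a difference when only one interval excludes zero, or no difference when the intervals overlap. Neither inference is sound.

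**Working it through.** **1. Gender coding.** Take a participant who is neither male nor female and meets none of the other five criteria.

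| Place | Gender element | Combined status |
|---|---|---|
| This Study | not male | yes |
| Other Measures | female | no |
| Subgroup Analyses, coding rule | not male | yes |
| Subgroup Analyses, indicator list | sex | depends on recorded sex |

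The other five elements agree apart from wording (migration history, migrant status). The narrower variable has no gender element and is unaffected.

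**2. Likely size of the unexposed stratum.** The article gives no prevalences, so these are assumptions, in the order gender, urbanicity, low SES, migration, ethnic minority, lower education. Under independence the unexposed share is the product of (1 − p).

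- Low (50/50/10/15/5/10%): 0.5 × 0.5 × 0.9 × 0.85 × 0.95 × 0.9 = 0.164, about 8 of 50; 84% positive.
- Middle (60/60/15/25/10/20%): 0.4 × 0.4 × 0.85 × 0.75 × 0.9 × 0.8 = 0.073, about 4 of 50; 93% positive. With 25 per arm, the binomial chance that at least one arm has fewer than 2 unexposed is 69%.
- High (75/80/25/35/15/30%): 0.25 × 0.2 × 0.75 × 0.65 × 0.85 × 0.7 = 0.015, about 1 of 50; 99% positive.

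At the other extreme, if the traits overlap fully, coverage equals the largest single prevalence: 50%, 60% and 80%, leaving 25, 20 and 10 unexposed. The narrower variable under independence is positive in 35%, 54% and 71%, so both its strata are populated.

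For self-report outcomes the extended model (Initial Signals of Efficacy) has six fixed coefficients: intercept, time, condition, baseline, condition × time and baseline × time. It adds a random intercept and correlated residuals. Four people with two post-baseline assessments supply at most 8 observations. The momentary models also carry random slopes with an unstructured covariance matrix.

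**3. What the strata give, and what a contrast adds.** The difference between two stratum effects has SE = √(SE₁² + SE₀²), so it can be derived. In one simulated least-squares example (50 participants, strata of 40 and 10), the difference between the stratum effects equalled the coefficient from the fully interacted model: 0.729 in both. The SE was 0.692 from separate fits and 0.599 from the single model, which pools the residual variance. That example does not extend exactly to mixed models with variance components fitted separately by stratum.

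**4. Precision of the contrast.** In SD units, with n per arm in each stratum, SE(d) = √(2v/n). Unadjusted, v = 1. Assuming a correlation of 0.6 between the two post-baseline measures and 0.36 of variance removed by baseline, v = (1 + 0.6)/2 − 0.36 = 0.44.

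At an even split n = 12.5 per arm, so the SE of the difference is √(2/12.5 + 2/12.5) = 0.566 and the half-width is 1.96 × 0.566 = 1.11.

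| Split (50 analysed) | Half-width, v = 1 | Half-width, v = 0.44 | Power for 0.5 SD (v = 1; 0.44) |
|---|---|---|---|
| 50/50 | ±1.11 | ±0.74 | 14%; 27% |
| 80/20 | ±1.39 | ±0.92 | 11%; 19% |
| 90/10 | ±1.85 | ±1.23 | 8%; 12% |

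With 42 analysed, close to the 85% retention threshold, the v = 1 half-widths are ±1.21, ±1.51 and ±2.02.

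**The case against.** The strongest reply is that objective 5 is itself a feasibility question. The distributions are described before any effect is estimated, so a near-empty stratum would be a finding and not a design failure. The plan already stratifies by a narrower variable without gender and urbanicity, and it calls all efficacy analyses exploratory. Minimum cell sizes and the exact contrast commonly sit in the analysis plan, which is preregistered but not shown.

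Most of this stands, and it limits the point. It does not remove it: the gender conflict is in the article's own text, the third step is unconditional as written, and the stated credibility criterion compares intervals by stratum.

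Three stronger readings are tempting and not supported.

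- A reader might infer that differential effects cannot be estimated. They can: the difference and its SE follow from two independent strata.
- A reader might infer that the combined variable will capture nearly everyone. That rests on assumed prevalences and independence. Full overlap gives 50% to 80%, and Recruitment allows participants from outside the region.
- A reader might infer that every non-binary participant changes group. Only those who meet none of the other five criteria do.

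**Conclusion.** The coding conflict is certain from the text. It probably affects few participants; the article gives no number. A small unexposed stratum for the combined variable is plausible, at about 1 to 8 of 50 under independence, but it depends on assumptions and could be 10 to 25 if traits overlap fully. Comparing intervals by stratum is a weaker method than reporting the contrast itself, although both draw on the same information. Naming the contrast corrects the inference but not the precision. With 50 participants its half-width is about ±1.1 SD at an even split unadjusted, or ±0.7 SD under the assumed adjustment gains, and it widens as the split becomes uneven. The point is worth correcting because objective 5 feeds the next trial. It does not touch the primary objective on recruitment.

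**What to change.** 1. Use one gender definition in This Study, Other Measures and Subgroup Analyses, and say whether gender or sex is the indicator described.
2. Estimate the subgroup difference from one model on all randomised participants, adding condition × group and group × baseline to the planned terms. Report the interaction and both subgroup effects with 95% CIs, led by the narrower marginalized variable.
3. State beforehand that the combined variable stays descriptive if its unexposed stratum is too small to fit the model. Any numerical cut-off is a judgement for the trial team; the documents supply no basis for a particular one.
4. State that the contrast is imprecise at this size and serves planning only.

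If the unshown analysis plan already fixes these points, aligning the article with it is enough. Data collection is complete and no new data are needed, so the cost is wording and a few model terms. The rule in item 3 should be settled before outcomes are examined by subgroup. The downside is that fewer stratum-specific estimates may be shown for the combined variable.
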